## Abstract

**Background::**

Severe and morbid obesity are increasing globally, particularly in women. As BMI increases, the likelihood of anovulation is higher. The primary aim of the EMOVAR clinical trial is to examine, over the short (16 weeks) and medium (12 months) term, the effects of a supervised physical exercise program (focused primarily on aerobic and resistance training) on ovarian function in women with severe/morbid obesity who have undergone bariatric surgery. Secondary objectives are to examine the effects of the intervention on chronic inflammation, insulin resistance, arterial stiffness, physical fitness, and health-related quality of life.

**Methods::**

This is a randomized controlled trial in which ∼40 female bariatric surgery patients, aged between 18 and 45 years old, will be included. Participants assigned to the experimental group will perform a total of 48 sessions of supervised concurrent (strength and aerobic) training (3 sessions/week, 60 min/session) spread over 16 weeks. Patients assigned to the control group will receive lifestyle recommendations. Outcomes will be assessed at baseline, week 16 (i.e., after the exercise intervention) and 12 months after surgery. The primary outcome is ovarian function using the Sex-Hormone Binding Globuline, measured in serum. Secondary outcomes are serum levels of anti-mullerian hormone, TSH, T4, FSH, LH, estradiol, prolactine, and free androgen index, as well as oocyte count, the diameters of both ovaries, endometrial thickness, and uterine arterial pulsatility index (obtained from a transvaginal ultrasound), the duration of menstrual bleeding and menstrual cycle duration (obtained by personal interview) and hirsutism (Ferriman Gallwey Scale). Other secondary outcomes include serum markers of chronic inflammation and insulin resistance (i.e., C-reactive protein, interleukin 6, tumor necrosis factor-alpha, leptin, glomerular sedimentation rate, glucose, insulin and the HOMA-IR), arterial stiffness, systolic, diastolic and mean blood pressure, body composition, and total weight loss. Physical fitness (including cardiorespiratory fitness, muscular strength, and flexibility), health-related quality of life (SF-36 v2) and sexual function (Female Sexual Function Index) will also be measured.

**Discussion::**

This study will provide, for the first time, relevant information on the effects of exercise training on ovarian function and underlying mechanisms in severe/morbid obese women following bariatric surgery.

**Trial registration number::**

ISRCTN registry (ISRCTN27697878).

## Introduction

1

The prevalence of severe/morbid obesity (body mass index; BMI ≥35 kg/m^2^) has increased globally in recent decades,^[1–4]^ being close to 7.5% in the United States.^[5]^ In Spain, figures show that the prevalence of morbid obesity (BMI ≥40 kg/m^2^) increased by more than 200% in the last 3 decades,^[3]^ being 1.39% in women (i.e., >300,000 cases) in 2016,^[6]^ and with specific areas of Spain presenting a prevalence of severe and morbid obesity (combined) of up to 10%.^[7]^ Cardiometabolic risk factors are significantly altered in patients with severe/morbid obesity, even compared with patients with type I obesity (BMI ≥30 and <35), both in men and women,^[7]^ which partially justifies the higher incidence of morbidity (e.g., hypertension, type 2 diabetes, metabolic syndrome, etc), cardiovascular events and cardiovascular^[8]^ and all-cause^[9,10]^ mortality (i.e., up to 30% higher compared to normal weight individuals^[10]^) observed in this population.

According to the National Statistical Institute (INE), the number of births in 2017 decreased by 4.5% compared to 2016,^[11]^ and by more than 20% compared to 2008. Severe/morbid obesity produces significant gynaecological problems including ovulatory problems,^[12]^ which contribute to the decline in birth rates. Increased adiposity is associated with irregularities in menstruation, anovulation, hirsutism, and polycystic ovary syndrome, among others,^[12,13]^ which results in significant problems with ovulating, subfertility and infertility^[13]^; this not only affects women's gynaecological health, but also their quality of life and potentially their relationship with a partner. The mechanisms that link obesity to ovarian function are not yet known in depth, although it appears that there is an alteration in the hypothalamus–pituitary–ovarian axis.^[14]^ Excess adiposity increases the aromatization of androgens to estrogen, decreasing the hepatic synthesis of sex hormone-binding globulin (SHBG).^[13,15]^ This increases levels of estradiol and circulating testosterone (raising the free androgenic index), and thus increases the risk of menstruation irregularities. Reduced pulsatility of luteinising hormone (LH) has been observed, which could reduce oocyte recruitment and quality and alter endometrial decidualization, which in turn could affect the function of the corpus luteum during the luteal phase^[16]^ and alter oocyte maturation.^[17]^ In addition, obesity appears to promote the accumulation of lipids in the oocyte, which activates the stress pathway in the endoplasmic reticulum, inducing mitochondrial dysfunction and increased apoptosis of the developing ovarian follicles.^[18]^

Many of the ovulatory problems observed in women with severe/morbid obesity may be mediated by a chronic pro-inflammatory status (excessive accumulation of pro-inflammatory cytokines)^[19]^ that favor, for instance, the incidence of polycystic ovary syndrome^[20,21]^ making ovulation difficult. In obese women, Jungheim et al observed noticeable alterations of inflammatory markers, such as C-reactive protein, leptin, or tumor necrosis factor alpha, in the follicular fluid.^[16]^ Furthermore, obesity is associated with vascular alterations and elevated arterial stiffness,^[22–25]^ which is associated with significant changes in uterine artery flow^[25]^ and could be related to ovulatory problems.

For many women with severe/morbid obesity, bariatric surgery^[26,27]^ is the first step towards a change in their lifestyle and quality of life, as it significantly reduces excess weight^[28]^ and promotes the remission of metabolic syndrome, hypertension or type 2 diabetes,^[29]^ which in turn significantly decreases the incidence of morbidity–mortality.^[30,31]^ Bariatric surgery seems to improve a woman's ovarian function by reducing the free androgen index, partially improving the luteal function,^[32]^ regulating the menstrual cycle (by increasing follicle-stimulating hormone [FSH] and LH, and decreasing testosterone and Dehydroepiandrosterone sulfate [DHEA-S]), improving conception rates and reducing the incidence of early abortions.^[33]^ However, other authors indicate that by increasing the rate of maternal malabsorption (depending on the surgical technique) and decreasing the ovarian reserve by decreasing levels of Anti-Müllerian hormone,^[34,35]^ fertility could continue to be compromised following bariatric surgery. Moreover, the success of bariatric surgery and the evolution of the patient in the short, (and above all) medium and long term is strongly determined by their post-operative lifestyle.^[36]^ About 50% of patients regain weight in the 24 months after surgery^[37]^ and may again have complications associated with severe/morbid obesity.^[38,39]^ It is therefore of great clinical and public health importance to study the effectiveness of complementary interventions aimed at improving the lifestyle of the obese patient from the first year of bariatric surgery in order to understand the effects of these changes in ovarian function and reproductive capacity, compared to the usual post-operative treatment.

Physical exercise following bariatric surgery has been shown to significantly improve cardiorespiratory fitness^[40]^ and muscular strength,^[41,42]^ to regulate autonomic nervous system dysfunction^[40,43]^ and to improve mitochondrial respiration at the muscular level^[44]^ as well as glucose metabolism.^[44,45]^ Our research group observed that being physically active is associated with a more favorable cardiometabolic profile in women with severe/morbid obesity,^[7]^ and has recently suggested^[46]^ that physical exercise can be a powerful predictor of the improvements observed in pain and physical function following bariatric surgery.^[47]^ Supervised physical exercise could also have positive effects on ovarian function following bariatric surgery. In women of reproductive age, exercise has shown to be effective in improving ovulatory cycles, ovulation and fertility, decreasing testosterone and the free androgen index, and increasing SHBG in the absence of obesity.^[48]^ In obese women, exercise similarly appears to increase the number of ovulatory cycles and improve fertility, despite absence of weight loss.^[49]^ For obese women with polycystic ovary syndrome, Palomba et al^[50]^ demonstrated that exercise reduces insulin-resistance in a more lasting way than diet (reducing the amount of adipose tissue and improving glucose metabolism in skeletal muscle), restoring ovulation in 65% of the participants.^[50]^ In this line, Coen et al,^[44,45]^ in a sample of 128 participants (88% women) with severe/morbid obesity undergoing bariatric surgery, demonstrated that partially supervised exercise increases insulin sensitivity with respect to a group receiving usual care, although there were no changes in weight loss. In conjunction, these results indicate that the effects of exercise on insulin resistance are, at least partially, independent of weight loss, and suggest that exercise could reduce the androgenic profile (free testosterone, dihydroepiandrostendione, and the free androgen index) and increase SHBG production, improving or even restoring ovulation.^[51]^ Hakimi et al^[52]^ systematically reviewed the effects of exercise on ovulation and concluded that 30 to 60 min/day of vigorous exercise is associated with a lower risk of anovulation, and that exercise can be used as a treatment for anovulation in overweight and obese women.

Other proposed mechanisms implicated in the relationship between obesity and reproductive problems, such as chronic inflammation^[53]^ or arterial stiffness,^[54]^ could also be significantly improved through exercise in this population. Recently, Stolberg et al^[55]^ found no improvement in inflammation following a training program initiated 6 months after bariatric surgery (70% women), although program adherence was clearly insufficient (i.e., only 59.4% of the participants attended 50% or more sessions) and the insufficient details about the intervention compromises replicability and the quality of the study.^[56]^ Therefore, the extent to which exercise, started immediately after surgery, can improve inflammation and arterial distensibility, and whether changes in these parameters can mediate possible improvements in women's ovarian function remain to be investigated.

For all of the above, studying the effectiveness of a supervised concurrent (strength and aerobic) exercise programme on the ovarian function of women undergoing bariatric surgery, both in the short (16 weeks) and medium (12 months) term, is of great clinical and social interest, especially considering the significant ovulatory problems that obesity confers. We postulate that a supervised evidence-based exercise program following the *Consensus on Exercise Reporting Template* (CERT),^[57,58]^ significantly improves ovarian function following bariatric surgery.

Thus, the main aim of the EMOVAR clinical trial is to examine, over the short (16 weeks) and medium (12 months) term, the effects of a supervised physical exercise program (focused primarily on aerobic and resistance training) on ovarian function in women with severe/morbid obesity who have undergone bariatric surgery, in comparison with usual care following bariatric surgery. Secondary aims are to examine the effects of the intervention on chronic inflammation and insulin resistance, arterial stiffness, physical fitness and health-related quality of life. We will also assess whether changes in inflammatory parameters, insulin resistance or arterial stiffness, induced by exercise, are associated with changes in ovarian function. Finally, the extent to which changes in body weight and composition, or changes in physical fitness (i.e., aerobic capacity and muscular strength), induced by the training program, are associated with changes in ovarian function will also be investigated.

## Material and Methods

2

### Study design and protocol registration

2.1

The EMOVAR study is a parallel-group randomized controlled trial (RCT) registered at the ISRCTN registry (ISRCTN27697878) on October 4, 2019, before the enrolment of participants begun (i.e., on October 15, 2019). The study protocol (version 1.0) was reviewed and approved by the Ethics Committee of the Torrecárdenas University Hospital (code RTI2018-093302-A-I00; 7/2019) on January 30, 2019.

### Recruitment and eligibility criteria

2.2

#### Recruitment

2.2.1

Participants will be recruited through the Bariatric Surgery Unit at Torrecárdenas University Hospital (the main referral hospital in the city of Almería, southern Spain) and Hospital Mediterráneo, consecutively one at a time, during the pre-surgery appointments. In both hospitals, the equipment, the criteria to indicate bariatric surgery, as well as the techniques performed, are identical. These two hospitals cover ∼90% to 95% of the bariatric surgeries performed in the entire province of Almería. Under normal conditions, ∼80 to 90 patients (∼70% women) attend the clinics (including both centres) annually, of which around 70 to 75 patients meet the bariatric surgery criteria and are eventually intervened.

#### Eligibility criteria

2.2.2

The inclusion and exclusion criteria are detailed in Table 1.

**Table 1 T1:**
[figure not shown]
Inclusion and exclusion criteria for selecting participants.

### Sample size

2.3

The number of patients needed was estimated based on the primary outcome—SHBG. At the time this protocol was conceived, there were no previous studies on the effects of physical exercise on ovarian function in women with severe/morbid obesity or after undergoing bariatric surgery. Therefore, the sample size was estimated using prior research on exercise effects in obese women,^[59]^ based on an expected increase in SHBG of at least 10 nmol/L in the EG compared to the CG. To detect a between-group change of 10 nmol/L (assuming a standard deviation equal to the expected effect), with a statistical power of 85% and an α error of 0.05, 36 women (n = 18 per group) will be needed. Anticipating a 10% follow-up loss, we will aim at recruiting ∼40 women. Adherence strategies will be implemented during the intervention program to minimize potential follow-up losses. If no participants are lost to follow-up, the final power of the study (with n = 40) for detecting the indicated effect would be 88.5%. In the absence of an accurate estimate for the expected standard deviation, Figure 1 represents the power curve for estimating the expected effect (the variation in the SHBG change between the EG and the CG of 10 nmol/L), considering different standard deviations and for a sample size of 36 (n ∼ 18 per group) or 40 (n ∼ 20 per group).

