### Statistical analysis

2.11

Despite randomization, the between-group baseline comparability will be checked. Normal distribution of continuous quantitative variables will be graphically inspected using histograms, and—when needed—normality tests will also be used. The between-group differences in the change (post–pre) in the primary and secondary effects (the main and secondary objectives 1, 2, and 3) will be analysed using a general linear model (in the case of significant deviation from normality, we will proceed with non-parametric techniques, such as quantile regression). The effect size (95% confidence interval) and the level of statistical significance will be displayed. In order to demonstrate the clinical efficacy of the supervised exercise program on ovarian function after bariatric surgery, the main analysis will be a per-protocol analysis (i.e., it will only include participants who attend at least 80% of the exercise sessions). Sensitivity analyses will be carried out using the intention-to-treat principle to check the robustness of the results. Missing data will be replaced using multiple account imputation. Despite the randomization, we will attempt to minimize potential confounding by adjusting for baseline values and other potential confounders. The association between changes in ovarian function with changes in the mechanisms involved (secondary objectives 4, 5, and 6) will be analysed using Pearson or Spearman correlations and/or regression analysis. The analyses will be conducted with Stata v.13.1 or superior (StataCorp LP, College Station, TX). Statistical significance will be set at *P* < .05.

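### The stated 85% and 88.5% power describe all followed-up women, not the per-protocol set (at least 80% attendance) named for the main analysis

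*Protocol article*

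**What the plan says.** Section 2.3 (Sample size) bases the calculation on the primary outcome, SHBG: "The number of patients needed was estimated based on the primary outcome—SHBG". The target difference is "based on an expected increase in SHBG of at least 10 nmol/L in the EG compared to the CG", with the standard deviation set by "assuming a standard deviation equal to the expected effect". The result is given as "with a statistical power of 85% and an α error of 0.05, 36 women (n = 18 per group) will be needed". The step from 36 to about 40 has one stated reason: "Anticipating a 10% follow-up loss, we will aim at recruiting" about 40 women. For the case in which nobody is lost, the power with 40 women "for detecting the indicated effect would be 88.5" per cent.

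Section 2.11 (Statistical analysis) makes the main analysis per-protocol and defines the set: "it will only include participants who attend at least 80% of the exercise sessions". Intention-to-treat is a sensitivity analysis.

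The protocol states no expected share of exercise-group women who will reach 80%. The only attendance figure in the document is in the Introduction and describes an earlier post-bariatric exercise trial: "only 59.4% of the participants attended 50% or more sessions".

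**The concern.** The sample size counts women who are followed up. The main analysis counts women who are followed up and, in the exercise group, also attended at least 80% of sessions. A woman can complete every assessment and still be removed by the attendance rule, and section 2.3 makes no allowance for her. Adherence strategies appear there only as a means of limiting follow-up losses. The multiple imputation in section 2.11 fills in missing values; it does not bring back women excluded by rule.

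The power quoted for the trial is thus the power of a different analysis set from the one on which the main conclusion will rest. If the main result is inconclusive, a reader who weighs it against 85% or 88.5% will credit the trial with more ability to detect 10 nmol/L than the main analysis may have had.

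**Working it through.** **Inputs.** Difference 10 nmol/L, SD 10 nmol/L (standardised difference d = 1), α 0.05, power 85%, equal allocation, 10% follow-up loss: all from section 2.3. Sidedness is not stated; two-sided reproduces the figures and is used here. Attendance rule of 80%: section 2.11. Share of exercise women reaching 80%: not given, so taken as a range of 60% to 100%. Controls have no exercise sessions, so the rule is read as removing exercise-group women only.

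**Reproducing the plan's figures.**
- n per group = 2(1.960 + 1.036)² / d² = 17.96, so 18 per group and 36 in total.
- Normal-approximation power = Φ(d√(n₁n₂/(n₁+n₂)) − 1.960). For 18 vs 18 this is Φ(3.000 − 1.960) = 85.1%. For 20 vs 20 it is Φ(3.162 − 1.960) = 88.5%.
- Recruitment: 36 / 0.90 = 40.

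All the stated figures are reproduced, for the numbers of women they use.

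**Applying the attendance rule.** The same formula is used with the exercise group reduced and the control group kept whole. The t column is an unadjusted two-sample noncentral t calculation with n₁ + n₂ − 2 degrees of freedom.

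| Follow-up loss | Share reaching 80% (assumed) | Exercise vs control | Normal approx. | Two-sample t |
|---|---|---|---|---|
| Planned 10% | 100% | 18 vs 18 | 85.1% | 83.0% |
| Planned 10% | 90% | 16 vs 18 | 82.9% | 80.6% |
| Planned 10% | 80% | 14 vs 18 | 80.1% | 77.5% |
| Planned 10% | 60% | 11 vs 18 | 74.3% | 71.2% |
| None | 100% | 20 vs 20 | 88.5% | 86.9% |
| None | 90% | 18 vs 20 | 86.8% | 85.0% |
| None | 80% | 16 vs 20 | 84.7% | 82.5% |
| None | 60% | 12 vs 20 | 78.2% | 75.5% |

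Worked example, 14 vs 18: √(14 × 18 / 32) = 2.806, and Φ(2.806 − 1.960) = 80.1%.

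**Slack.** With the planned 10% loss there is none: excluding one woman (17 vs 18) gives 84.1% by the same normal approximation. With no follow-up loss, power stays close to the 85% target until about 4 of 20 exercise women are excluded, but any exclusion takes it below 88.5%.

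**The case against.** The strongest reply is that section 2.3 contains no arithmetic error and that the loss may be small. Both parts stand. Every stated figure is reproduced, and the 88.5% is expressly conditional on nobody being lost. At 90% or 80% attainment with the planned loss, power falls by about 2 or 5 points from the figure without exclusions; only towards 60% does it fall by more than 10.

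A reader might take the 59.4% from the earlier trial as this trial's benchmark and conclude that power cannot exceed about 75%. The document does not support that. The figure refers to a 50% attendance threshold in a programme begun 6 months after surgery, and the Introduction cites it as clearly insufficient adherence. Here the programme begins soon after surgery, every session is individual and supervised, and adherence support is planned. The figure is a reason to show a range and no more.

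A reader might also infer that 83.0% and 86.9% are the true power of the planned model. They are unadjusted figures, whereas section 2.11 plans adjustment for baseline values. If baseline correlated 0.25 with the change in SHBG (an assumption), t-based power would be 85.2% at 18 per group and 88.9% at 20. The gap of about 2 points between t and normal is secondary, and section 2.3 itself admits that it lacks an accurate SD.

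Finally, the effect may be larger among attenders. At 11 nmol/L (an assumption), 14 vs 18 gives 84.8% by t. That could offset the loss, but section 2.3 does not count on it.

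None of these points removes the mismatch: the stated power is for a set of women other than the one in the main analysis.

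**Conclusion.** The point holds as a mismatch between sections 2.3 and 2.11, not as a miscalculation. The 85% and 88.5% are right for all followed-up women with the full 10 nmol/L difference. They carry over to the per-protocol main analysis only if every exercise-group woman attends at least 80% of sessions, a condition the protocol does not state.

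The size of the shortfall cannot be fixed from the document. Over an assumed 60% to 90% attainment with the planned follow-up loss, power lies between 74.3% and 82.9% by the normal approximation, or between 71.2% and 80.6% by unadjusted t. This rests on d = 1, a two-sided 0.05 test, exclusions from the exercise group only, no gain from baseline adjustment and no larger effect in attenders. That an exclusion lowers power below the matching stated figure, at the same effect and SD, is firm; by how much is not. It should be corrected, but it does not call the design into question.

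**What to change.** In section 2.3, keep both figures but state their condition: 85% and 88.5% refer to all followed-up women, with the full 10 nmol/L difference and no dilution from non-attendance. The 88.5% need not be removed.

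Add a short table of power for the per-protocol main analysis by share of exercise-group women reaching 80% attendance, labelled as a range of assumptions. T-based figures are preferable: unadjusted, they start at 83.0% (18 per group) and 86.9% (20 per group) with no exclusions, with a note that baseline adjustment could raise them. If the earlier trial's 59.4% is mentioned, give it as the reason for showing a range and note its 50% threshold.

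The cost is a few lines of text and a less favourable stated figure. No extra patients are needed.
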